### Identification of C(E)TRs

We will undertake keyword searches in the EHR of people with intellectual disability or autism who meet the study eligibility criteria to identify each community C(E)TR event and the date on which it occurred. Search terms will be ‘Care and Treatment Review’, ‘Care Education and Treatment Review’, ‘CTR’ and ‘CETR’. The search interface does not recognise punctuation or wildcards. We will create a list of people whose health records contain any of these text strings and will review the context of the positive mention to ascertain true instances of C(E)TR meetings, along with the date that the meeting was held. We will label a C(E)TR meeting as having taken place where there is evidence that a meeting has occurred and where a date of the meeting is available. We expect there will be mentions of the search terms which do not correspond to a C(E)TR meeting taking place, for example, where a possible future C(E)TR is flagged. Some mentions of the search terms will be false positives (eg, spe*ctr*um, ECG), and such irrelevant cases will be discounted.

To ensure reliability of identification, two members of the research team will independently review records of 100 eligible patients where C(E)TR search terms have been identified. Cohen’s Kappa will be calculated to test the agreement between the two raters.^10^ If inter-rater reliability is acceptable (Cohen’s kappa >0.6), the raters will work independently and only flag cases that cannot easily be determined. If initial inter-rater reliability is inadequate (Cohen’s kappa <0.6), we will discuss and refine the method of ascertaining whether a keyword mention represents a C(E)TR meeting using a series of test cases. The raters will reconvene periodically to double-review a subset of records to ensure that practice remains consistent. We will retain key excerpts of anonymised text from the EHR as exemplars of mentions of C(E)TRs; a selection of these will be reported for transparency, and the examples can also be used to train any additional members of the research team who interrogate the records.

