### Classification of C(E)TRs as community or inpatient

Information on all psychiatric inpatient spells will be extracted for those in the cohort. We will place this alongside the dates of recorded C(E)TRs to categorise the C(E)TR as a community C(E)TR (ie, occurring when the person was living in the community) or an inpatient C(E)TR (ie, occurring when the person was admitted to a psychiatric hospital). All analyses that follow will be performed on community C(E)TRs.

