### Exposure

Exposure will be defined as the community C(E)TR.

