### Matching a control group

We will match between one and five controls, who will not have a community C(E)TR, per patient who has a C(E)TR. Eligibility will be a diagnosis of intellectual disability or autism and having received a continuous period of community care within SLaM services for at least a year between 1 January 2015 and 31 December 2023. Matching will be based on age (±3 years), sex (male/female) and diagnosis (intellectual disability with/without autism, or autism without intellectual disability). Controls should be under an active episode of community care and not be an inpatient on the index date of their matched case. They must also have been under SLaM services for a similar total duration of their matched case (±2 years). Matching with replacement will be applied to ensure every case has an appropriate match according to these criteria. A pseudo-index date for each control will be assigned and will be the same as the index date of their matched case.

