### Sensitivity analyses

Sensitivity analyses will be carried out on the causal framework to probe the robustness of the applied model. During the C(E)TR identification process, we will identify patients for whom a community C(E)TR was suggested, where there was no evidence that a C(E)TR did in fact occur. These are to be included in the pool of control patients in our main analysis. Exploratory sensitivity analyses will: (1) Re-assign these patients to the C(E)TR group, and use the date in the record when a C(E)TR was suggested (or soon thereafter) as the index date and/or (2) Directly compare the main C(E)TR group with the ‘C(E)TR suggested’ group.

Some patients may have multiple community C(E)TRs while under follow-up. These will be treated as separate events in the main analysis (if the C(E)TRs are at least 6 months apart). Patients who have multiple C(E)TRs may have a different profile of baseline characteristics than those who receive only one. This may lead to preintervention differences in the C(E)TR versus no C(E)TR groups that cannot be sufficiently controlled for using the propensity scoring method. A sensitivity analysis will be performed on the subgroup of patients who only had one C(E)TR (vs no C(E)TR), improving sensitivity to the causal effect of a single C(E)TR.

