### Identifying cases and controls

Using the review of clinical records of eligible patients previously described, we will measure whether each patient had a community C(E)TR within 6 months prior to their psychiatric hospital admission. We will form two groups: those who had a pre-admission community C(E)TR, and those who did not.

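### People with evidence of a C(E)TR but no recorded date have undetermined exposure, yet by default they count as unexposed in both sub-studies

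*Protocol article*

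**What the plan says.** Under *Identification of C(E)TRs*, raters read each keyword mention in context and label a meeting as held only where there is "evidence that a meeting has occurred and where a date of the meeting is available". Both conditions must be met.

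The date then does further work. *Classification of C(E)TRs as community or inpatient* compares it with inpatient spells: "We will place this alongside the dates of recorded C(E)TRs to categorise the C(E)TR as a community C(E)TR". In sub-study 1 it is the index date, and "Exposure will be defined as the community C(E)TR". In sub-study 2 it decides whether the meeting fell in the 6 months before admission.

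For the comparison groups, *Matching a control group* (sub-study 1) states: "We will match between one and five controls, who will not have a community C(E)TR, per patient who has a C(E)TR". It adds: "Matching with replacement will be applied to ensure every case has an appropriate match according to these criteria". *Identifying cases and controls* (sub-study 2) forms two groups, "those who had a pre-admission community C(E)TR, and those who did not", and has no undetermined category.

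*Sensitivity analyses* deals with one kind of uncertain exposure: a community C(E)TR was suggested, "where there was no evidence that a C(E)TR did in fact occur". Those people are controls in the main analysis and are re-examined in exploratory analyses. *Missing data* says that the design leaves the intervention and the outcome fully observed.

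**The concern.** The rule foresees meetings for which there is evidence but no date, and then says nothing about the people concerned. If they count as unexposed, each comparison group may contain people who had the intervention. Where their meeting was a qualifying one and worked as dated ones do, the contrast shrinks.

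The plan is also uneven. It re-examines people for whom a C(E)TR was only suggested, but not people whose record contains positive evidence of a meeting. The article itself warns that few events may leave the study underpowered, so avoidable dilution deserves attention.

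**Working it through.** **Where an evidenced but undated person goes**

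1. *Labelling.* The second condition of the rule fails, so no C(E)TR is labelled.
2. *Exclusions.* None of *Study eligibility criteria*, *Matching a control group*, the sub-study 2 *Inclusion and exclusion criteria* or *Identifying cases and controls* removes the person.
3. *Sub-study 1.* With no labelled C(E)TR, the person is eligible as a control. Because matching is with replacement, the same person can be used more than once.
4. *Sub-study 2.* The two groups are exhaustive, so the person falls in the comparison group.
5. *Sensitivity analyses.* The suggested group requires absence of evidence that the meeting occurred. This person has such evidence and is outside it.
6. *Missing data.* Since exposure is taken as fully observed, no method for missing exposure is planned.

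**Illustration of size**

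The article gives no undated share, exposed share or sample size, so there is no figure to reproduce. Every input below is an assumption.

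Let u be the share of *true, in-window community* C(E)TRs that lack a date, p the true exposed share of the hospital cohort, k the number of controls per case, and m the truly exposed share of the comparison group.

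*Sub-study 2:* m = u·p / [(1 − p) + u·p]

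| u | p | m |
|---|---|---|
| 0.05 | 0.10 | 0.005/0.905 = 0.6% |
| 0.10 | 0.10 | 0.01/0.91 = 1.1% |
| 0.20 | 0.20 | 0.04/0.84 = 4.8% |
| 0.30 | 0.30 | 0.09/0.79 = 11.4% |
| 0.30 | 0.50 | 0.15/0.65 = 23% |

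*Sub-study 1*, if each undated person is drawn exactly once: m = [u/(1 − u)]/k

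- k = 5: from 0.0526/5 = 1.1% (u = 0.05) to 0.4286/5 = 8.6% (u = 0.30)
- k = 1: from 5.3% to 43%

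A large control pool would lower these values, and repeated use of the same control could raise them.

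If undated meetings have the same effect and the same baseline risk as dated ones, a difference in means or risks retains the fraction 1 − m. That is 99% to 77% over the sub-study 2 range. For a hazard ratio this is only a rough guide.

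*Power.* Assume 100 cases, five controls each, and admission risks of 30% and 45%, in a simple two-proportion comparison. The control risk becomes 0.45(1 − m) + 0.30m. Power is 80.5% at m = 0, 76.4% at m = 5% (control risk 44.25%) and 71.8% at m = 10% (43.5%).

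If u is taken instead as the undated share of *all* recorded meetings, the formulas assume that every undated meeting was an in-window community one, and m is then too high.

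**The case against.** A reader might infer that people known to be exposed are placed in the comparison groups. The documents do not support that. Exposure means a community C(E)TR and, in sub-study 2, one within 6 months before admission. The plan decides both from the date. An undated meeting shows only that some C(E)TR took place. It may have been an inpatient one, or too early or too late to count, so some of these people are correctly unexposed.

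A reader might also infer that both primary comparisons must move towards no difference. That needs undated and dated meetings to share the same effect and baseline risk. If undated people are at higher risk, simple dilution no longer describes the result. Nor do the documents show that the problem is worst in the hospital cohort: they give no cohort size or C(E)TR frequency, and that is where undated inpatient meetings are most plausible.

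Three further points can be made for the plan:

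- **The date requirement is necessary for the exposed group.** In sub-study 1 it sets the index date and both observation windows. This stands.
- **The control definition could be read as barring these people,** and raters flag cases that are hard to determine. But the labelling rule decides who counts as having a C(E)TR, and the article does not say what follows from a flag.
- **Coding of residual cases may sit in a fuller document.** That would hold if the article were merely silent. It fixes a two-part rule and an exhaustive two-group split, which together produce the default.

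A blanket exclusion in sub-study 2 would also be unsafe. Longer stays give more opportunity for an inpatient C(E)TR. Dropping everyone with an undated meeting would select on an event after admission that is related to the outcome, and would tend to shorten stays in the comparison group.

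**Conclusion.** The point holds as a gap in the exposure rule. People with evidence of a C(E)TR but no date have undetermined exposure. By default they count as unexposed in both sub-studies, no sensitivity analysis covers them, and the plan describes exposure as fully observed.

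The default is read from the labelling rule and the absence of any exclusion; the article does not state it. Some dilution of both comparisons is the likely effect, but it is not certain. Its size cannot be estimated from the documents and may be trivial if few meetings are undated. The percentages above show only how it depends on assumed inputs.

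**What to change.** 1. Add an evidenced-but-undated code to the planned record review. Use the context and the note dates to class each such meeting as community, inpatient or undetermined, and as before or after admission. A note dated before admission shows that the meeting it records came first; a later note does not settle the order.
2. In sub-study 1, exclude from the control pool people with a possible community C(E)TR of unknown date.
3. In sub-study 2, exclude from the comparison group only people whose meeting could have been a community C(E)TR in the 6 months before admission. Keep those whose meeting was evidently inpatient or after admission.
4. Report the number in each class.
5. Add a sensitivity analysis that counts as exposed those whose text indicates a community meeting, with the note date as an approximate date.
6. Qualify the statement in *Missing data* that the intervention is fully observed.

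The cost is one more code in a review already planned, a few sentences of text, one sensitivity analysis and the loss of a few potential controls. Some undetermined meetings excluded under step 3 may still have been inpatient ones, which is a further reason to report the numbers.

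### The kappa check on C(E)TR coding is run on patients with any keyword hit, so easy negatives such as 'spectrum' may carry it past 0.6 despite poor agreement on genuine mentions

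*Protocol article*

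**What the plan says.** All of the coding rules stand in the Protocol article under Identification of C(E)TRs. The terms are given as: "Search terms will be ‘Care and Treatment Review’, ‘Care Education and Treatment Review’, ‘CTR’ and ‘CETR". Entry to the review list needs only one hit: "We will create a list of people whose health records contain any of these text strings". Two limits of the search are acknowledged: "The search interface does not recognise punctuation or wildcards", and "Some mentions of the search terms will be false positives (eg, spe*ctr*um, ECG), and such irrelevant cases will be discounted". The plan also expects a harder kind of negative: "We expect there will be mentions of the search terms which do not correspond to a C(E)TR meeting taking place", for instance when a C(E)TR is only proposed for the future.

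For reliability, "two members of the research team will independently review records of 100 eligible patients where C(E)TR search terms have been identified". If kappa exceeds 0.6, "the raters will work independently and only flag cases that cannot easily be determined". If it is lower, the method is discussed and refined on test cases. The raters also come back together from time to time to double-review some records; the number of records, the frequency and the level of agreement required are not given.

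Study eligibility criteria makes autism one of two qualifying diagnoses. The strengths and limitations list says that the number of people with a community C(E)TR in the data is unknown.

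**The concern.** The hits are of two kinds. A genuine mention of a C(E)TR needs judgement: was the meeting held, or only suggested, and on what date? An in-word hit such as 'spectrum' needs none, and any two raters will call it negative. The reliability sample is defined by having a hit of either kind. Each in-word hit in it adds an agreed negative, which raises kappa and says nothing about the hard cases.

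The result decides whether the remaining coding is done by one rater per record. That coding defines the exposure in both sub-studies and the index date in sub-study 1. It also separates held meetings from those merely suggested, and patients with only a suggested C(E)TR belong to the control pool in the main analysis (Sensitivity analyses section). A held meeting that is missed can therefore place an exposed person among the controls.

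**Working it through.** **Inputs from the plan.** 100 double-rated patients; a point estimate of kappa above 0.6 as the gate; sampling frame of any search-term hit. The plan gives no precision or prevalence figure behind the 100 or the 0.6, so there is no stated figure to reproduce.

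**Assumptions.** The documents give no share of genuine mentions among hits and no share of real meetings among genuine mentions, so both are varied. Both raters call every in-word hit negative and have equal margins.

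**Formula.** kappa = (po − pe)/(1 − pe), where po is observed and pe is chance agreement.

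**1. Dilution.** Take kappa 0.40 on genuine mentions, half of them real meetings. The cell proportions (both yes / one only / other only / both no) are then 0.35 / 0.15 / 0.15 / 0.35. Fill the sample to 100 with in-word hits, all agreed negatives.

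- 20 genuine mentions: 7 / 3 / 3 / 87. po = 0.94; pe = 0.10² + 0.90² = 0.82; kappa = 0.12/0.18 = 0.67.
- 40 genuine mentions: 14 / 6 / 6 / 74. po = 0.88; pe = 0.20² + 0.80² = 0.68; kappa = 0.20/0.32 = 0.625.
- 100 genuine mentions: 35 / 15 / 15 / 35. po = 0.70; pe = 0.50; kappa = 0.40.

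Simulated chance of passing the gate (200,000 draws per setting) for the same raters:

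| Genuine mentions in 100 | Overall kappa | Chance of passing |
|---|---|---|
| 10 | 0.68 | 65% |
| 20 | 0.67 | 66% |
| 40 | 0.625 | 61% |
| 100 | 0.40 | 1% |

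**2. Sensitivity to the assumptions.** With k the kappa on genuine mentions, p the share of these that are real meetings and f the share of the sample that are genuine mentions, the same algebra gives

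overall kappa = 1 − (1 − k)(1 − p)/(1 − pf).

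Whenever f is below 1 this exceeds k, so under this model the direction is always upwards. The size varies.

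- k = 0.30, p = 0.5: 1 − 0.35/0.90 = 0.61 at f = 0.20, but 1 − 0.35/0.80 = 0.56 at f = 0.40, which fails.
- k = 0.50, p = 0.5: 0.72 at f = 0.20 and 0.69 at f = 0.40.
- k = 0.40, f = 0.20: at p = 0.3, 1 − 0.42/0.94 = 0.55 (fails); at p = 0.7, 1 − 0.18/0.86 = 0.79 (passes).

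**3. Imprecision.** Suppose 3 records are agreed positive, 2 and 1 discordant, and 94 agreed negative. po = 0.97; pe = (5 × 4 + 95 × 96)/10,000 = 0.914; kappa = 0.056/0.086 = 0.651. With a standard error of 0.188 the 95% CI is 0.651 ± 0.368, or 0.28 to 1.0 after truncation. This passes, although the raters agreed on only 3 of the 6 records that either called a C(E)TR.

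Simulated for a true kappa of 0.6 and n = 100, by assumed share of real C(E)TRs in the sample:

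| Share real | 95% range of the estimate |
|---|---|
| 5% | −0.01 to 0.92 |
| 10% | 0.27 to 0.84 |
| 20% | 0.38 to 0.79 |
| 50% | 0.44 to 0.74 |

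**The case against.** Several points on the other side have weight.

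- **The shares are unknown.** A reader might infer that about half the cohort is autistic, that most hits are irrelevant, or that the 100 will hold only a handful of real C(E)TRs. The documents support none of these: they name two diagnoses without a split, speak of some false positives, and call the number of C(E)TRs unknown. At 20% or more real, the imprecision is moderate. This stands.
- **Low prevalence does not by itself let weak raters through.** In a simple model with rater sensitivity 0.7 and specificity 0.995 on all records, the chance of passing is 37% at 2% real, 48% at 5%, 54% at 10%, 59% at 20%, 52% at 30% and 20% at 50%. There is no steady trend, so a contrast of two chosen prevalences proves little. This stands; the point rests on dilution.
- **Any cut-off can turn on one record.** With balanced records, 41/10/9/40 gives 0.62 and passes, while 40/10/10/40 gives 0.60 and does not. That is no fault peculiar to this gate.
- **There are other safeguards.** Hard cases are flagged, records are periodically double-reviewed, and a sensitivity analysis deals with patients for whom a C(E)TR was only suggested. These help in part. Flagging depends on a single rater noticing the doubt, and the re-review has no stated size or threshold.
- **Irrelevant hits may be dropped first.** The plan says that they will be discounted, and says so before it describes the 100. Sampling after that step is a possible reading, but it is not stated, and the sample is defined by search terms having been identified. If that is the intent, one sentence settles the matter.
- **Date.** A meeting is counted only if a date is available, so having a date is part of the rating. Agreement on which date is not mentioned; this is a minor reporting point.

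**Conclusion.** The concern holds in a limited form. As the sampling frame is written, the gate may release raters to single rating although they agree poorly on the mentions that need judgement. Under the stated assumptions, raters with kappa 0.40 on genuine mentions pass 61% to 66% of the time when 10 to 40 of the 100 are genuine, against 1% when all are. The upward direction holds throughout the model; whether kappa crosses 0.6 depends on shares that the documents do not give, and in some settings it does not. The added imprecision matters only if real C(E)TRs are few in the sample.

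A reader might go further and conclude that the check cannot support single rating at all. The documents do not bear that out: the share of irrelevant hits is unknown, and flagging, periodic double review and the sensitivity analysis give some protection. It is an inexpensive improvement to a rule that the protocol itself fixes, and it should be made before coding starts.

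**What to change.** Under Identification of C(E)TRs, state that irrelevant in-word hits are discounted first. Then draw the 100 double-rated patients from those whose record holds a genuine C(E)TR mention: either full phrase, or CTR or CETR as a stand-alone term. If fewer than 100 such patients exist, use them all. Apply the 0.6 threshold to that sample and report kappa with its 95% CI. Also report the proportion of agreed meetings for which both raters recorded the same date, because that date sets the index date in sub-study 1.

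If the 100 are all genuine mentions and about half are real meetings, the estimate has a standard deviation of 0.08 at a true kappa of 0.6 (95% range 0.44 to 0.75). Raters at 0.4 would pass about 1% of the time and raters at 0.8 about 99.9%.

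The cost is some pre-screening, since the search tool may not be able to isolate a stand-alone CTR. If 20% of hit patients have a genuine mention, about 100/0.20 = 500 must be screened to find 100; at 40%, about 250. The plan already has the context of hits reviewed, so much of this is a change of order. Kappa may look less favourable, which would lead to the refinement step that the plan already provides.

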### Classification of C(E)TRs as community or inpatient

Information on all psychiatric inpatient spells will be extracted for those in the cohort. We will place this alongside the dates of recorded C(E)TRs to categorise the C(E)TR as a community C(E)TR (ie, occurring when the person was living in the community) or an inpatient C(E)TR (ie, occurring when the person was admitted to a psychiatric hospital). All analyses that follow will be performed on community C(E)TRs.

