## Methods and analysis

### Study setting

Data will be obtained from the South London and Maudsley (SLaM) NHS Foundation Trust. SLaM is one of the largest providers of secondary mental healthcare in Europe, with a diverse catchment area of approximately 1.3 million people who live in the south London boroughs of Lambeth, Southwark, Lewisham and Croydon. Mental health services provided by SLaM include specialist teams for children and adolescents with mental illness and/or neurodevelopmental conditions, community teams for adults, including specialist teams for those with intellectual disability, and mainstream and specialist inpatient wards across different sites. The Trust has implemented a full EHR since 2006, and the SLaM NIHR Maudsley Biomedical Research Centre Case Register contains the clinical records of >5 00 000 patients.^4 5^ Unless otherwise stated, data will be extracted up to an end date of 31 December 2024. The protocol for this study was finalised in July 2025. Data extraction is anticipated to be complete by September 2025 and data analysis by December 2025.

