### Data source and linkage

The Clinical Record Interactive Search (CRIS) is a research tool that enables analysis of de-identified EHRs. Patient-level data are extracted from structured fields and through interrogation of unstructured free text (eg, clinical letters and reports) using validated Natural Language Processing (NLP) applications. Available variables include socio-demographic information, neuro-psychiatric signs and symptoms, interventions (medication, psychological therapy), hospital admissions and contacts with professionals and teams (eg, doctors, allied health professionals). We will link data obtained from the SLaM clinical record with Hospital Episode Statistics (HES), a national dataset curated by NHS Digital that includes details of all general hospital inpatient admissions, outpatient appointments and attendances to A&E in England.^6^ Data linkage takes place in a secure data safe haven.^7^

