### Outcome

The primary outcome will be psychiatric hospital admission (treated as a binary variable) at any time within 6 months after the index date (online supplemental table 2).

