#### Economic analysis

A partial economic evaluation will assess the cost impact of community C(E)TRs on secondary healthcare use. The primary outcome will be total secondary healthcare cost per patient, comparing those who received a community C(E)TR with those who did not. Service use data will be derived from CRIS and HES. Database accessibility and relevant resource use variables will be reviewed to determine feasibility. If both CRIS and HES are used, discrepancies for the same patient will be checked manually. Due to the linkage, the end date for the HES data extraction will be 31 March 2024. For HES data, the HRG Grouper and Spell Converter will be used to classify activity and define spells of care. Unit costs will be based on NHS Reference Costs and costs published by the Personal Social Services Research Unit (PSSRU).^23^ Mean cost differences and 95% CI will be estimated using non-parametric bootstrap regression (5000 replications), adjusting for baseline costs and covariates from the main analysis. Service-specific utilisation will be summarised descriptively without formal comparisons, to focus on total cost and avoid multiple testing issues.

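### A C(E)TR held in another provider's hospital can be classed as a community C(E)TR, because the only stated rule compares dates with inpatient spells whose provider coverage is not given

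*Protocol article*

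**What the plan says.** All references are to the protocol article.

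- **Label.** The section Classification of C(E)TRs as community or inpatient begins: "Information on all psychiatric inpatient spells will be extracted for those in the cohort". It continues: "We will place this alongside the dates of recorded C(E)TRs to categorise the C(E)TR as a community C(E)TR" or as an inpatient one. No other criterion follows, and all later analyses are restricted to community C(E)TRs. The label therefore defines exposure in both sub-studies.
- **Sources.** Under Study setting: "Data will be obtained from the South London and Maudsley (SLaM) NHS Foundation Trust". Under Data source and linkage, the one external source is HES, described as "a national dataset curated by NHS Digital that includes details of all general hospital inpatient admissions, outpatient appointments and attendances to A&E in England". Its stated role is in the Economic analysis section: "Service use data will be derived from CRIS and HES", subject to a feasibility check.
- **Manual review.** Under Identification of C(E)TRs, the raters "will review the context of the positive mention to ascertain true instances of C(E)TR meetings, along with the date that the meeting was held". The setting of the meeting is not among the items they record.
- **Outcome of sub-study 1.** "The primary outcome will be psychiatric hospital admission (treated as a binary variable) at any time within 6 months after the index date". No provider is named; the sentence points to a supplementary table that is not shown.
- **Completeness.** The Missing data section says that, by design, there are no gaps in the intervention or the outcome.

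**The concern.** The project concerns only C(E)TRs held in the community, so separating them from inpatient C(E)TRs is basic to the question. A date rule is only as good as the list of spells behind it. If a psychiatric stay elsewhere is not on that list, a C(E)TR held during the stay falls outside every recorded spell and can be taken as a community event.

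The same gap then acts twice. It creates a false exposure, and it hides the hospital stay that should count in the outcome. The two errors occur in the same people, and only in the treated group. Controls may also have unseen stays, but they are not selected because of an event that took place during one. At stake is a spurious protective effect in an analysis that the article presents as causal.

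**Working it through.** The article gives no sample size, event rate or share of C(E)TRs held elsewhere, so there is no figure to reproduce. The arithmetic below is illustrative and every rate in it is an assumption.

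**Inputs (assumed)**
- No true effect; control group unaffected; treated events equally weighted.
- Risk of a recorded psychiatric admission in correctly labelled events: p_pre = 25% and p_post = 30%, a true change of +5 points.
- m = share of labelled community C(E)TRs that were in fact held in an unrecorded hospital stay, with no recorded admission in the six months after.

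**Route A: recorded SLaM spell in the pre-window, then transfer out (scored 1, then 0)**

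Observed change = (1-m)·p_post - [(1-m)·p_pre + m]. Subtracting the true change gives a shift of -m·(1 + p_post - p_pre) = -1.05m.

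**Route B: stay unseen in both windows (scored 0, then 0)**

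Shift = -m·(p_post - p_pre) = -0.05m.

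**Fallback: logistic model on the post-period only (Stage 2 section)**

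Spurious risk difference = -m·p_post = -0.30m, whatever happened before the index date.

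| m | Route A (points) | Route B (points) | Fallback (points; odds ratio) |
|---|---|---|---|
| 2% | -2.1 | -0.1 | -0.6; 0.97 |
| 5% | -5.25 | -0.25 | -1.5; 0.93 |
| 10% | -10.5 | -0.5 | -3.0; 0.86 |

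**Dependence on the background risks, at m = 5%**
- 20% before and after: Route A -0.05 × 1.00 = -5.0 points; Route B exactly 0.
- 30% before, 20% after: Route A -0.05 × 0.90 = -4.5 points; Route B -0.05 × (-0.10) = +0.5 points, against the C(E)TR.

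**Mixture of routes.** If a fraction t of the misfiled events follows Route A and the rest Route B, the shift at 25%/30% is -m·(t + 0.05). With m = 5% and t = 0.2 (also assumed) it is -0.05 × 0.25 = -1.25 points.

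The main analysis is thus sensitive to Route A and nearly insensitive to Route B. The fallback is affected by both.

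**The case against.** Four counter-arguments deserve weight.

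1. **The text says all spells.** A reader might infer that the label uses SLaM spells only. The classification section does not say so. It sets no limit by provider, and letters and reports searched through CRIS may mention stays elsewhere. The restriction is an inference from the sources described. What stands is that none of those sources is said to hold other providers' psychiatric stays systematically, so the word is not backed by a named source.

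2. **Raters read the context.** A reader might also infer that every C(E)TR held elsewhere will be mislabelled. That is too strong. The article defines a community C(E)TR by where the person was living, and a rater may see that the meeting was on a ward. What stands is that the review is stated to establish only that the meeting occurred and when. No stated rule carries the setting into the label.

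3. **The large shifts need a chain of events.** Route A requires a SLaM stay in the previous six months, a transfer out, a C(E)TR there that is dated in the SLaM notes, a setting that goes unnoticed, and no SLaM stay in the next six months. This stands in full. It is why a general claim that misfiled events produce an apparent benefit in the main analysis is not supported. For sub-study 2 no bias has been worked out, and its exclusion of admissions within six months of a previous discharge would remove many people who return after a transfer.

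4. **An article condenses.** Extraction details may well sit in a fuller document. But the article itself states both the classification rule and the claim of completeness, and these two do not fit the sources it describes.

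**Conclusion.** The point holds in a limited form. The only stated criterion for the exposure label is a comparison of dates with psychiatric inpatient spells, and the described sources give no systematic view of such spells at other providers. A C(E)TR held in another provider's hospital can therefore enter the treated group as a community event while the stay is absent from the outcome. The Missing data section's assurance about exposure and outcome is not supported by what the article describes.

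The size cannot be judged from the document, because the share of affected events is not given. Under the assumed 25%/30% risks, each 1% of events on the transfer route moves the main estimate by about -1.05 points. Each 1% unseen in both windows moves it by about -0.05 points, and that smaller bias vanishes or changes sign with other background risks. In the post-only fallback, every such case without a later recorded admission scores as no admission, about -0.3 points per 1% at a 30% post-period risk. The -10.5 point figure is the end of an assumed range with every misfiled event on the transfer route; it is not an estimate of the bias in this study.

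The reason to act is that this misclassification falls on the treated group alone and is cheap to prevent.

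**What to change.** 1. During the manual review, have raters record from the same text where the person was living at the time of the meeting: community, SLaM ward, or other hospital.
2. Class any C(E)TR that the text places in a hospital as inpatient, whatever the date comparison says.
3. Where text and dates conflict and cannot be resolved, leave the event out of the main analysis and add it back in a sensitivity analysis.
4. State the source and provider coverage of the psychiatric inpatient spells, for both the label and the outcome.
5. Qualify the Missing data statement: exposure and outcome are observed only as far as those sources reach.

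The cost is one extra field in a review that is already planned, and the loss of a small number of events from the main analysis. The number reclassified would also show how common the problem is, which the article cannot.
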